## Introduction

### Young People Placed in Juvenile Institutions

The Swedish National Board of Institutional Care (Statens institutionsstyrelse, SiS) runs special residential homes and provides individually tailored compulsory care for young people with psychosocial problems, substance abuse and aggressive antisocial behaviors. Care is provided under the terms of the Care of Young Persons (Special Provisions) Act (LVU) (1990:52) and the Secure Youth Care Act (LSU) (1998:603). The social services of the municipalities are responsible for handling and placing these young people into SiS, as well as taking care of their needs and support after their release from SiS. SiS runs 23 special residential homes in Sweden that currently holds about 700 adolescents in need of special, compulsory care (Personal communication with SiS statistic unit, January 2021).

Every year, the Social services commit over a thousand young people between 15 and 21 years old to SiS's juvenile institutional care due to drug abuse, criminal activity, and/or other socially destructive behaviors. According to SiS (1) the average length of special care in 2019 was 164 days per young person, amounting to ~206,000 care days a year. In 2019, Swedish municipalities alone spent 1.44 billion Swedish crowns (SEK) on young people's care committed to juvenile institutions.

Within this population of children and young adults, the majority has at least one but most often several coexisting psychiatric diagnoses (2), even though the primary reason for the compulsory care is their antisocial behavior, which hampers individual development. The most common diagnosis for both young males and females is Attention-Deficit Hyperactivity Disorder (ADHD), followed by Substance Use Disorder and Post-Traumatic Stress Disorder (PTSD). During the peculiar circumstances of the year 2020, due to the COVID-19 pandemic, a substantial proportion of Swedish adolescents reported more substance use (3) suggesting a possible increased pressure on SiS services in following years.

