About half of the young people in the SiS juvenile institutional care report having experienced depression for a longer period of time, attention difficulties, and/or severe anxiety/tension. Almost every other female (47%) and more than 10% (13%) of males has attempted suicide. More than one in three has been the victim of physical and/or psychological abuse by a parental figure. About 40% report having witnessed violence against someone close to them, and nearly half of the females have been victims of sexual abuse (4).

A majority of the young people in SiS care have failed at school, have difficulties keeping up with the teaching, and/or have poor attendance. Their challenges are often complicated, and their environment (family relations, the circle of friends) has often had a substantial impact on their current situation.

The special residential homes run by SiS are the only treatment facilities in Sweden that have the right to forcibly detain individuals who have been taken into compulsory care according to the LVU Act. This right encompasses the options to place individuals under lock and key and/or physically restrain them if they pose a danger to themselves or others. In 2019, physical restraint was used 1,152 times in the residential homes run by SiS (1). According to SiS, most of these events involved a small number of young people and the common factor was a low functioning level, neuropsychiatric disorders, and comorbid psychiatric illness.

Recent research has shown that this population of adolescents has an increased need for improved and integrative treatments. A 3-year follow-up study of institutionalized young people found dramatically increased rates of criminal recidivism, use of inpatient care, and untimely death among young people in institutional care compared to an age-matched general population group (5). The past year's (COVID-19 pandemic) dramatic changes resulted in increased stress, insecurity, fear of illness, risk of an imbalance between school-work and private life, and social isolation. Adolescents reply to these type of traumatic events with an increased incidence of anxiety-, eating disorders, depression, self-harm, suicide, and illegal substance use. A general increase in crime, where violence in close relationships and cyberbullying are some of the most frequent problems, is predicted. These are realities that high schools, social services, health cares, and families have to be prepared to face.

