## Methods

### Participants

Computer required sample size analysis for repeated measures ANOVA within-between interaction, with an effect size of 0.25 [medium effect size; average from effect sizes in changes by yoga in previous studies (9, 25)], a power of 0.80, an alpha error probability at 5%, for two groups (yoga and comparison) and two measurements (pre-and post-intervention) suggested a sample size of 34 for each sex.

We aim to collect complete data from at least 34 participants of both sexes (34 male and 34 female clients) to perform gender-specific analyses. Gender analyses will only be performed, if this number of participants can be reached.

Based on previous experience working with participants within correctional settings, we know that the attrition rate can reach 50%; therefore, our aim is to include approximately 120 participants.

Three institutions at the South West in Sweden have at this stage declared interest in participating in the study. Data collection is planned to take place for one and a half years' time, based on an estimated three months per institute (Figure 1). This three months period includes spreading advertisements and information about the study, collecting informed consents, six weeks of intervention (including pre- and post-intervention tests), and time for qualitative interviews to assess individual experiences of yoga classes. As the average time spent within SiS is calculated to be eight months, we will be able to perform intervention and data collection in each participating institute twice, six months apart during the planned data collection period (one and a half years) (Figure 1).

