## Discussion

While there is a growing body of evidence in favor of the unique and significant positive effects of yoga as a form of complementary care for vulnerable populations (such as people with psychiatric conditions and/or people in correctional settings), there is a lack of research measuring the effects of yoga in the population of adolescents in residential/institutional care. The Swedish National Board of Institutional Care (Statens institutionsstyrelse, SiS) offers compulsory care for young people who manifest psychiatric disorders, substance use disorder and criminal behavior (2). The average age of an institutionalized young (fe)male is 16 years old, and (s)he meets the criteria for at least one psychiatric diagnosis. The most frequent diagnoses are ADHD, Substance Use Disorder, PTSD, Conduct Disorder, and Autism Spectrum Disorder. Depression and anxiety are usually co-existing diagnoses. One in four of these young people has attempted suicide. This population of adolescents has an increased need for effective treatments that can prevent the development of persistent mental ill-health, substance dependence, recidivistic criminal behavior, social marginalization, and untimely death. The young people's mental ill-health in SiS is substantial and extensive medical and psychological treatments are provided during their stay. SiS's goal and vision is, that the young people undergoing various SiS treatment programs should have gained by the end of their stay at SiS increased resources to live their lives without crime and abuse.

According to a follow-up study (5) today's institutional care is not sufficiently effective. Half of these young people have a history of at least one inpatient treatment episode, 60% are reconvicted for criminal acts, and 3% die within three years of their release from the institution.

Therefore, the planned study's impact can be measured from the aspects of the individual, the organizations, and the society.

Disruptive behaviors and high levels of psychological distress often hamper treatment responsivity. The suggested positive effects of yoga (decreased levels of psychological distress and less aggressive and antisocial behavior) may result in increased treatment responsivity, which may reduce the number of care days. This positive outcome may entail considerable benefits in terms of significantly decreased economic burdens on SiS and the society.

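### At the 50% attrition cited as its basis, the target of about 120 inclusions gives 60 completers, not the 68 needed for gender-specific analyses

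*Protocol article*

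**What the plan says.** All the figures stand in the Participants section of the protocol article.

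- **Sample size per sex.** A repeated measures ANOVA calculation (within-between interaction, two groups, two measurements) is run "with an effect size of 0.25 [medium effect size; average from effect sizes in changes by yoga in previous studies (9, 25"), with "a power of 0.80, an alpha error probability at 5"%. It returns 34 for each sex.
- **Completer target.** "We aim to collect complete data from at least 34 participants of both sexes (34 male and 34 female clients"). That is 68 people with complete data.
- **Inclusion target.** "we know that the attrition rate can reach 50%; therefore, our aim is to include approximately 120 participants".
- **Rule.** Analyses by gender go ahead only if 34 of each sex is reached. The Data Analysis section repeats this threshold, and says that the data are otherwise pooled without results by gender. It also restricts the analysis to participants with complete data after attrition.

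**The concern.** The inclusion target is presented as following from the attrition figure, yet 120 halved is 60 and the completer target is 68. Because only complete data are analysed, attrition reduces the analysis set one for one.

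What is at stake is the gender-specific aim. The 68 was set so that each sex could be analysed separately. At the attrition level that the plan names as its reason for 120, the plan's own rule switches those analyses off. Readers of the protocol, and those planning recruitment at the three institutions, would take 120 to be a number that secures them.

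**Working it through.** **Inputs.** From Participants: f = 0.25, power 0.80, alpha 0.05, two groups, two measurements, 34 per sex, attrition up to 50%, about 120 inclusions. From Data Analysis: completers only, pooling if 34 per sex is not reached. The pre-post correlation (rho) is not given and has to be assumed.

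**1. The plan's 34 per sex.** Noncentral F with lambda = f² × N × m/(1 − rho), df1 = 1, df2 = N − 2. With rho = 0.5 and N = 34, lambda = 0.0625 × 34 × 2/0.5 = 8.5 and power is 0.807; with N = 32 power is 0.781. So 34 reproduces, as a total over both groups within one sex. It depends on the assumed correlation:

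| Assumed rho | N needed |
|---|---|
| 0 | 66 |
| 0.3 | 46 |
| 0.5 | 34 |
| 0.6 | 28 |
| 0.7 | 22 |

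**2. Completers needed.** 34 + 34 = 68.

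**3. Inclusions needed at 50% attrition.** 68/(1 − 0.50) = 136. The common shortcut of multiplying by one plus the dropout rate gives 68 × 1.5 = 102. Neither gives 120.

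**4. What 120 delivers at 50%.** 120 × 0.50 = 60 completers. The shortfall is 68 − 60 = 8 completers, or 136 − 120 = 16 inclusions.

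**5. Effect on the gender rule.** Both sexes can reach 34 only if there are at least 68 completers. With 60, at least one sex is below 34 whatever the split; an even split gives 30 and 30.

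**6. Attrition at which 120 is just enough.** 1 − 68/120 = 0.433, and then only if completers divide evenly by sex.

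**7. Meeting the target on average against meeting it.** As an illustration, assume equal numbers of each sex are included and dropout is independent between participants. The chance that both sexes reach 34 completers is the square of a binomial tail:

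| Included (per sex) | Attrition | Expected completers | Chance both sexes reach 34 |
|---|---|---|---|
| 120 (60) | 50% | 60 | about 3% |
| 120 (60) | 45% | 66 | about 20% |
| 120 (60) | 43% | 68.4 | about 33% |
| 120 (60) | 40% | 72 | about 56% |
| 120 (60) | 30% | 84 | about 98% |
| 136 (68) | 50% | 68 | about 30% |

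**8. Pooled comparison.** 60 completers exceed the calculated 34, so on the plan's own calculation the pooled analysis keeps its power at 50% attrition.

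**The case against.** **50% is a ceiling and 120 is approximate.** The first part stands: the text says how high attrition can go and gives no expected rate, so a reader who infers that the plan will miss its target goes beyond the document. But the 50% is the only attrition figure offered for this design, and the sentence derives 120 from it. If a lower rate was in mind, it is not stated. The word approximately does not bridge the gap, since 136 is 16/120 = 13% above 120.

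**The plan already covers a shortfall.** This stands and limits the weight of the point. The pooling rule is fixed in advance and the pooled comparison survives. A reader might infer that the whole study is underpowered; the plan's own figures do not show that. A requirement above 60 arises in the table above only at an assumed correlation of zero (66), which is not the value that reproduces the plan's 34.

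**Sex balance.** A reader might combine "Almost every other female (47%) and more than 10% (13%) of males has attempted suicide" with "One in four of these young people has attempted suicide", solve 0.47p + 0.13(1 − p) = 0.25 for about 35% females, and conclude that far more than 136 inclusions are needed. The documents do not support this. The two statements are not shown to share a source or year, and the overall figure is rounded. Reading it as 20% to 30% gives 21% to 50% females, which includes an even split. Nothing is said about the sex mix of the three participating institutions.

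**Length of stay.** A reader might also see a contradiction between "As the average time spent within SiS is calculated to be eight months" in Participants and "the average length of special care in 2019 was 164 days per young person" in the Introduction (164/30.4 = 5.4 months). The two may be different measures. About 206,000 care days divided by 164 is about 1,256 young people, so the 164 can be read as care days per person within one calendar year, while eight months may describe a whole stay. Either figure exceeds the three-month block at each institution. No error is demonstrated.

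**Conclusion.** The point holds in a narrow form. The inclusion figure of about 120 does not follow from 68 completers and 50% attrition: it gives 60, a shortfall of 8 completers or 16 inclusions. If attrition reaches 50%, the gender-specific analyses are lost under the plan's own rule, whatever the split between the sexes. This rests only on the protocol's figures. The probabilities in the working also assume equal inclusion by sex and independent dropout, and serve as illustration.

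The consequence is confined to the analyses by gender. The figure should be corrected, but the error does not undermine the pooled primary comparison and is not of the highest severity.

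**What to change.** Preferred: keep about 120 and add a sentence to Participants. It should say that 120 inclusions yield about 60 completers at 50% attrition, that gender-specific analyses are then not expected, and that 34 per sex is reached on average only if attrition is at most about 43% with completers evenly split by sex. This costs one sentence and no participants.

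Alternative: state that 50% attrition implies about 136 inclusions, 68 per sex. This costs 16 more inclusions and should carry the caveat that it meets the target only on average, with about a 30% chance that both sexes reach 34 under the illustration above. Giving 136 as a guarantee would replace one overstated figure with another.

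### About 120 enrolled cannot yield 34 completers of each sex at the plan's own 50% attrition, and no enrolment target is set by sex

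*Protocol article*

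**What the plan says.** Under Methods, Participants, the sample size is computed for a "repeated measures ANOVA within-between interaction, with an effect size of 0.25", and the calculation "for two groups (yoga and comparison) and two measurements (pre-and post-intervention) suggested a sample size of 34 for each sex". The aim is then put as complete data from 34 male and 34 female clients, and gender analyses are made conditional on reaching that number. The same section notes that attrition in correctional settings can be as high as 50% and draws the enrolment figure from this: "our aim is to include approximately 120 participants". That is one total; no number is given for either sex.

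The inclusion criterion offers the study to every young person who arrives, so nothing in recruitment steers the sex mix. Under Data Analysis, only complete data are analysed. If 34 of each gender are not reached, the data are pooled and no gender-specific results are given.

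No sex mix is stated anywhere. Two statements bear on it indirectly. The Introduction says: "Almost every other female (47%) and more than 10% (13%) of males has attempted suicide". The Discussion says: "One in four of these young people has attempted suicide".

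**The concern.** A minimum that must be met in each of two strata is governed by the scarcer stratum and cannot be secured by a total alone. Here the total is below the sum of the two minima once the stated attrition is applied, and the article's own background figures hint that one sex is clearly in the minority.

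At stake is the gender-specific analysis, which is the stated basis for the sample size. If either sex falls short, the plan's own rule removes that analysis and all gender-specific results. The pooled comparison of yoga with other activity survives.

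**Working it through.** **Inputs.** From Methods, Participants: effect size f = 0.25, power 0.80, alpha 0.05, two groups, two measurements, 34 completers per sex, attrition up to 50%, about 120 enrolled. From the Introduction: suicide attempts in 47% of females and 13% of males. From the Discussion: one in four overall. The pre-post correlation is not stated; 0.5 is assumed.

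**Step 1: the 34 per sex.** For the within-between interaction with N subjects and m measurements, the noncentrality is f² × N × m / (1 − ρ), with 1 and N − 2 degrees of freedom. With f = 0.25, m = 2 and ρ = 0.5, the smallest even N with power of at least 0.80 is 34 (power 0.807; N = 32 gives 0.781). The plan's figure reproduces and carries no slack.

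**Step 2: the 120.** Completers needed: 34 + 34 = 68. Enrolment at 50% attrition: 68 / (1 − 0.5) = 136, so 120 does not reproduce. Conversely, 120 × 0.5 = 60 completers, or 30 per sex if even. To have 34 completing females among 60, females must be 34/60 = 57% of the sample, which leaves 26 males. No split works. The total of 120 yields 68 completers only if attrition is at most 1 − 68/120 = 43.3%, and then only with an exactly even split.

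**Step 3: the sex mix suggested by the article.** Let F be the female share. Solve 0.47F + 0.13(1 − F) = 0.25:

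F = (0.25 − 0.13) / (0.47 − 0.13) = 0.12 / 0.34 = 35.3%.

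An even split would give an overall rate of (47 + 13)/2 = 30%. Since one in four is rounded, 22.5% and 27.5% are tried as well; that window is an assumption.

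**Step 4: consequence for females.** Enrolled = 120F. Completing at 50% = 60F. Break-even attrition = 1 − 34/(120F). Total needed without regard to sex at 50% attrition = 68/F. The last three rows are exact binomial probabilities with n = 120 and success probability F × (1 − attrition).

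| Overall rate read as | 22.5% | 25% | 27.5% |
|---|---|---|---|
| Female share F | 27.9% | 35.3% | 42.6% |
| Females among 120 | 33.5 | 42.4 | 51.2 |
| Females completing at 50% attrition | 16.8 | 21.2 | 25.6 |
| Break-even attrition | none | 19.7% | 33.6% |
| Total needed at 50% attrition | 244 | 193 | 160 |
| P(at least 34 females), 20% attrition | 0.07 | 0.53 | 0.93 |
| P(at least 34 females), 30% attrition | 0.01 | 0.21 | 0.67 |
| P(at least 34 females), 50% attrition | <0.001 | 0.003 | 0.04 |

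At the central share, male completers at 50% attrition are 60 × 0.647 = 39, so the male minimum is met and females are the limiting group.

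**Step 5: would a larger total repair it?** At 136 enrolled, 136 × 0.353 × 0.5 = 24 female completers. The total would then be right and the female minimum still missed.

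**The case against.** The strongest reply is that the female share is inferred. The article gives no sex mix, the overall rate in the Discussion is rounded and carries no citation of its own, and nothing shows that it comes from the same sample as the sex-specific rates. At best it describes the whole service (23 homes), whereas participants come from three interested institutions and consent is voluntary. This stands. A reader might infer that the plan's figures prove a one-third female population, or that the plan assumes half are female. The documents support neither: the first is a conditional inference, and the article states no split at all.

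A reader might also infer that the female target is almost certain to fail. That holds only near the upper attrition figure. The article says attrition can reach 50%, not that it will. At the central share the chance of success is about even at 20% attrition, and at the upper share it is about two in three at 30%.

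It can further be said that the plan foresees the shortfall: the gender analysis is conditional and the fallback is fixed in advance. The 60 pooled completers exceed the 34 from the same calculation. This limits the harm to losing the gender-specific analysis. It does not make 120 agree with the requirement from which it is said to follow.

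Finally, enrolment detail may sit in a fuller protocol. But the article itself gives the minimum per sex, the attrition and the total, and the three do not fit together.

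**Conclusion.** The point holds in two parts of different strength.

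The firm part rests on the Participants section alone. At the stated upper attrition, about 120 enrolled give about 60 completers where 68 are needed, and no division by sex gives 34 of each. The enrolment figure is 16 short of 136, and even 136 would suffice only with an even split.

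The conditional part assumes that the suicide-attempt rates share a source and that the three institutions resemble the service overall in sex mix and consent. Females are then roughly 35% (28 to 43%) and the limiting group: about 21 completers (17 to 26) against 34 at 50% attrition. The target is missed in expectation from about 20% attrition (from no attrition at all at the low share; from 34% at the high one). This part shows why a larger total alone may not be enough. It does not show what the sex mix will be.

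**What to change.** In Participants, replace the single total with an enrolment requirement per sex, 34 / (1 − attrition), which is 68 of each at 50%. Give the expected sex mix of the participating institutions and keep a recruitment tally by sex.

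If 68 females are not attainable, say in both Participants and Data Analysis that the gender-specific analysis is not expected to be reached. Then justify the sample size on the pooled analysis, with sex as a covariate or stratum.

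Male recruitment should not be closed to balance the sexes: the inclusion criterion offers the study to all arrivals, and males still count in the pooled analysis.

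Cost: restating the figure needs only wording and a tally, no extra participants, and a less favourable statement about the gender analysis. Pursuing 68 females does need more enrolment: at least 136 in all, and about 193 if the share is near 35% and all arrivals continue to be accepted.
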